#### Data collection

The health care providers based in the wards from where we will collect data will be informed about the study. They will identify patients who may be eligible and refer them to the RA for a second round of eligibility screening. The RAs shall provide potential participants with information about the study, obtain written informed consent, then administer the University of California, San Diego Brief Assessment of Capacity to Consent (UBACC) [42] to assess participant comprehension of the consent process.

RA’s will administer a) standardized questionnaire to collect demographic and clinical variables (age, gender, address, education, date of symptom onset) from the patients. We will collect demographic information in the form of age, gender, address and education from care givers. b) Feasibility measures (number of eligible participants who accept to enroll in the study, number of participants who are retained in care over study duration, number of participants who adhere to prescribed intervention, duration of recruitment of participants, reasons for decline to enroll in the study as well as reasons for dropping out of the study), c) MINI to confirm a diagnosis, d) Young Mania Rating Scale (YMRS) [43] for individuals with bipolar illness or Positive and Negative Symptoms of Schizophrenia Scale (PANSS) [44] for individuals with schizophrenia spectrum disorders to assess symptom severity e) World Health Organization Disability Assessment Schedule, f) Internalized Stigma of Mental Illness scale to assess for stigma, g) a medication adherence measure to assess for adherence h) Illness Management and Recovery (IMR) [45] scale to document the ability of patients to manage their illness and (i) care giver burden using the short version of the burden scale for care givers (BSFC) [46].

#### Blinding participants and RA to the study arm

Participants will be randomly assigned to the study arms. The RA and participants will all be blinded to the study arm they will be allocated before consent. VHTs will deliver 6 psycho-education sessions (1 per month) to participants in intervention arm and their family members at the participant’s residence. The PI and RAs will sit in some of the sessions during the first 2–3 sessions of data collection to ensure fidelity to the manual. We will conduct 5 exit focus group discussions with patients and family members to assess acceptability to the use of the manual. Participants in the control arm will get usual treatment. RA’s will schedule participants from both arms for an assessment using the same instruments at weeks 4, 12 and 24 at the clinic. We will have a separate set of RA’s for the intervention arm and another for the control arm to ensure blinding of the RA.

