### Study measurements

Trained RA will administer the following standardized questionnaires to all participants (see Table 1 below). All study questionnaires will be translated into Luganda, the commonly spoken local language at the study site.

We will document the number of participants who agree to provide written informed consent; we will record the reasons for declining to consent. We will use standardized forms to record the number of participants who will return to the clinic for monthly review as well as those who will complete the psycho-education sessions (intervention arm only).Demographic and clinical parameters: We will (a) document the age, gender, physical address, contact information, marital and employment status, education level, date/month/year of onset of current illness. We will document whether the participant lives within a catchment area of ministry of health supported VHT; we will separately contact the VHT and get their details. We will also request for information from the next of kin for future contact in the event of a loss to follow-up. (b) we will document the age of onset of symptoms, duration of illness before accessing hospital care (acute if it is ≤ 6 months of onset and chronic if it is ≥2 years), whether the participant has received prior treatment for the psychosis (traditional or faith healers), whether the patient had a say in the choice of antipsychotics that was prescribed to them.We will administer the UBACC [42] to assess participant’s capacity to provide informed consent.The M.I.N.I 7.0.2 [40] psychosis, depression, bipolar affective disorders, substance use disorder, PTSD and generalized anxiety modules will be used to confirm the presence of a psychoses, and other CMD. The MINI has been used in multiple Ugandan study settings including the Neuro-GAP project, although it is yet to be validated for use in these settingsSymptom severity assessed using the YMRS [43] or PANSS [44]. Both the YMRS and PANSS have been used in Ugandan study settings although it is yet to be validated for use in these settingsThe presence of medication side effects will be assessed using the modified version of the Glasgow Antipsychotic Side Effects Scale (GASS)The World Health Organization Disability Assessment Schedule Version 2 (WHODAS 2.0) will be used to assess the level of social and occupational functioning of participants. There is limited data about the use of the WHODAS in Ugandan populations.Adherence to antipsychotics will be measured using the medication adherence rating scale (MARS) for psychosis [47].We will document mortality from any causes in the participants using the WHO verbal autopsy scale.illness management ability will be assessed using the IMR [45].The care giver burden will be measured using the short version of the burden scale for care givers (BSFC) [46].

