### The intervention

After discharge, the program manager will link the participants with a VHT nearest to them. The participants (randomized to the intervention arm) will be informed during the consent procedure that they will undergo 6 psycho-education sessions (1 per month) together with a family member at the participant’s residence. The VHTs and participants will meet and schedule appointments for the next engagements. This shall be done on a case by case basis. Some psycho-education sessions could take place in the patient’s residence, others in the nearest public space (school or church or mosque compounds). We will document where the majority of these sessions happen. This will help us document feasibility. The PI and RAs will sit in some of the sessions during the pilot phase of data collection to ensure fidelity to the manual.

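### Giving each arm its own research assistants does not blind them, and it makes assessor set and treatment arm the same variable for the secondary efficacy outcomes

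*Protocol article*

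**What the plan says.** The section on blinding participants and RA provides for one set of RAs "for the intervention arm and another for the control arm to ensure blinding of the RA". The only other blinding statement there concerns the time before enrolment: "The RA and participants will all be blinded to the study arm they will be allocated before consent". That describes concealment of the coming allocation. It does not cover the ratings made after it.

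On outcome assessment, the same section says "RA’s will schedule participants from both arms for an assessment using the same instruments at weeks 4, 12 and 24 at the clinic", and Study measurements says "Trained RA will administer the following standardized questionnaires to all participants". RAs therefore administer every scale used for efficacy. Data analysis plans then compares the arms on mean adherence, stigma, illness management and PANSS or YMRS scores, with a Bonferroni correction.

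RAs also come into contact with the intervention. The blinding section says "The PI and RAs will sit in some of the sessions during the first 2–3 sessions of data collection", and The intervention says "The PI and RAs will sit in some of the sessions during the pilot phase of data collection to ensure fidelity to the manual". Only the intervention arm has sessions. Data collection also has RAs record how many participants adhere to the intervention.

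**The concern.** The stated purpose of the arm-specific sets is to blind the RA, and the arrangement works against that purpose. An RA whose caseload is a single arm can infer it, and attending sessions or recording adherence to them reveals it outright.

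The second consequence does not depend on what the RA knows. When one set scores all intervention participants and another scores all controls, a difference in scoring habits between the sets looks exactly like a treatment effect. Randomization gives no protection, because the difference arises after allocation. A rater term in the model cannot recover it, because raters are nested in arms.

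What is at stake is the preliminary efficacy estimate. Sample size estimation says the data will yield an effect size for planning a powered trial, and that figure would carry any scoring shift with it.

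**Working it through.** The protocol gives no figure for agreement between RAs and no formal power calculation, so there is nothing to reproduce. The following is illustrative.

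**Inputs from the protocol.** 40 per arm (Abstract, Methods); 80% retention (Hypothesis), so n = 0.8 × 40 = 32 per arm; four efficacy outcomes and three visits (Data analysis plans); Bonferroni correction, number of tests not stated.

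**Assumptions.** No true effect; outcome variance 1; k RAs per arm with equal caseloads m = n/k; between-RA intraclass correlation ρ of 0.05 or 0.10; two-sided test at 5%, or at 0.05/12 = 0.42% if Bonferroni covers 4 × 3 = 12 tests.

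**Formulas, RAs nested in arm.**
- Variance inflation of an arm mean: DE = 1 + (m − 1)ρ.
- Expected sample variance within an arm: s² = (1 − ρ) + ρ × n/(n − 1) × (1 − 1/k).
- False-positive rate: 2 × [1 − Φ(z / √(DE/s²))], with z = 1.960 at 5% and 2.865 at 0.42%.

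**Two RAs per arm (m = 16).**
- ρ = 0.05: DE = 1 + 15 × 0.05 = 1.75; s² = 0.95 + 0.05 × 32/31 × 0.5 = 0.976; √(1.75/0.976) = 1.339. At 5%: 1.960/1.339 = 1.464, giving 14.3%. At 0.42%: 2.865/1.339 = 2.14, giving 3.2%.
- ρ = 0.10: DE = 1 + 15 × 0.10 = 2.50; s² = 0.90 + 0.10 × 32/31 × 0.5 = 0.952; √(2.50/0.952) = 1.621. At 5%: 1.960/1.621 = 1.209, giving 22.7%. At 0.42%: 2.865/1.621 = 1.77, giving 7.7%.

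Simulating the two-sample t-test (200,000 runs per setting) gives 14.1% and 22.3% at 5%, and 3.0% and 7.2% at 0.42%. The normal formula is slightly high.

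**Range over the assumed number of RAs, formula, 5% test.**

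| RAs per arm | ρ = 0.02 | ρ = 0.05 | ρ = 0.10 |
|---|---|---|---|
| 1 | 12.7% | 23.2% | 35.8% |
| 2 | 8.7% | 14.3% | 22.7% |
| 3 | 7.4% | 11.0% | 16.9% |

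**Fixed shift.** If the two sets differ by 0.3 SD, the standardized difference is 0.3/√(2/32) = 1.2. The rejection rate is Φ(1.2 − 1.960) + Φ(−1.2 − 1.960) = 22.4% at 5%, and 4.8% at 0.42%.

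**Effect on the estimate.** The scoring shift between sets has SD √(2ρ/k). With two RAs per arm this is √0.05 = 0.22 SD (ρ = 0.05) or √0.10 = 0.32 SD (ρ = 0.10). More participants per RA do not reduce it.

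**RAs crossed over arms.** With one or two RAs per arm merged into a shared pool and caseloads balanced, the simulated rate at 5% is 4.0% to 4.9% (n = 32 or 40 per arm). RA differences then cancel from the arm contrast.

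**Can baseline data reveal a shift?** Table 1 lists PANSS/YMRS at baseline and follow-up, but MARS and IMR at follow-up only, so for those two it provides no baseline that could show a difference. For PANSS/YMRS it depends on which RAs score baseline, which is not stated. A difference that arises only at follow-up cannot be separated from treatment on any scale.

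**The case against.** The strongest reply is that this is a pilot whose primary objective is feasibility, with efficacy secondary and called preliminary. Much of that stands. Recruitment is settled before allocation and is untouched. Retention would be affected only if one RA set pursued its participants harder, and Community tracing sets one procedure for all participants. A reader might infer that the primary objective is compromised; the article does not support that. The reply does not save the effect size meant for the powered trial.

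A reader might also infer that every RA-administered outcome is biased. The text shows exposure to bias of unknown size and direction. Exposure is greatest for interviewer-rated PANSS/YMRS and smaller where the RA records the participant's own answers. Nor does the article show that agreement between RAs is poor. Lack of local validation is a different matter, the bachelor's-level description is attached only to the RA doing the MINI interview, and RAs receive four days of training.

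The session-attendance evidence is limited. It covers some early sessions, the pilot phase could mean the five test participants excluded from the analysis, and nothing says that observers score the same participants.

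Finally, one could suppose that neither set is told which arm it serves. Even then RA set and arm coincide, and the confounding remains. A fuller protocol may add detail, but the sentence is an explicit design choice with a stated purpose, and nothing else in the article offsets it.

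**Conclusion.** The point holds for the secondary efficacy outcomes. As written, the arrangement does not blind RAs and confounds RA set with treatment, and analysis cannot undo a scoring difference that arises at follow-up.

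The size cannot be derived from the protocol. With 32 per arm, no true effect, two RAs per arm and ρ of 0.05 or 0.10, false positives are about 14% or 22% for an unadjusted 5% test. It would be wrong to read these as this trial's error rates: the number of RAs and ρ are assumed, and a Bonferroni correction is planned. Over an assumed 12 tests the rates are about 3% or 7% per test against a nominal 0.42%, so the correction lowers the rate without removing the inflation.

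**What to change.** Replace the sentence on separate RA sets with the following provisions:
- One common pool of RAs, not told the allocation, scores outcomes in both arms, with each RA's caseload balanced over arms.
- RAs who sit in on sessions, or who record session attendance or adherence to the intervention, do not score outcomes for those participants. Crossing RAs over arms removes the confounding but does not blind them, so this separation is also needed.
- Participants are asked not to disclose their arm to the assessor.
- RA ID is recorded with every assessment so that it can be fitted as a factor.

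The cost is some scheduling effort and a division of tasks among the existing RAs. If arm-specific sets have to stay, withdraw the claim that they ensure blinding, and state the confounding of assessor with treatment as a limitation wherever the efficacy estimates or the effect size for the powered trial are reported.

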### Participant identification and recruitment

#### Identification

Health care workers in the different wards and out-patient departments of Butabika Hospital will be informed about the study. Trained RA shall liaise with the clinicians to identify potential participants for recruitment at the time of admission to the wards. RA’s will then assess participants who are due for discharge (patients with a clinical response to medications) for possible enrollment and provide them with information about the study. Patients who access care at the out-patient clinic (who may not be admitted) but are eligible will also be approached by the RA for enrollment.

#### The informed consent procedure

The RA’s will invite potential participants to take part in the study and obtain written informed consent. During the consenting process, the purpose of the study will be described further, the procedures will be explained, the benefits and risks of taking part in the study will be outlined. Upon demonstrating understanding and being given a chance to ask questions, the potential participant will then provide a witnessed, signed or thumb print consent. Caregivers will also be required to provide written informed consent, since we will collect demographic information from them.

#### Assessing the capacity to consent

We will administer the University of California, San Diego Brief Assessment of Capacity to Consent (UBACC) [42] instrument to assess whether the participants have understood the consent process. The UBACC will be translated into Luganda, the commonly spoken local language at the study site. The UBACC is a 10-item scale comprised of 3 factors that evaluate understanding, appreciation and reasoning. It has been used in the Ugandan setting for the Neuro-GAP project, although it is yet to be culturally adapted for use in these settings. A score of less than 14.5 on three separate occasions indicates that the participant has not understood what the study is all about. Such participants will not be recruited but will be given a chance to return at a later date for recruitment (within a week). We will record the number of participants who fail the UBACC at baseline and can’t be recruited and those who do so after being invited a week later.

We will ask participants to provide us with their demographic information (age, gender and education level) and examine whether there are significant differences between participants who are able to consent and those who are not. Participation in this study is completely voluntary. The patient has the right to withdraw at any time during the study, including at follow-up. We will document the reasons for withdrawal. Each interview is anticipated to last a minimum of 120 minutes—there will be 2–3 breaks at 40 minute intervals in between the interviews.

### Study measurements

Trained RA will administer the following standardized questionnaires to all participants (see Table 1 below). All study questionnaires will be translated into Luganda, the commonly spoken local language at the study site.

We will document the number of participants who agree to provide written informed consent; we will record the reasons for declining to consent. We will use standardized forms to record the number of participants who will return to the clinic for monthly review as well as those who will complete the psycho-education sessions (intervention arm only).Demographic and clinical parameters: We will (a) document the age, gender, physical address, contact information, marital and employment status, education level, date/month/year of onset of current illness. We will document whether the participant lives within a catchment area of ministry of health supported VHT; we will separately contact the VHT and get their details. We will also request for information from the next of kin for future contact in the event of a loss to follow-up. (b) we will document the age of onset of symptoms, duration of illness before accessing hospital care (acute if it is ≤ 6 months of onset and chronic if it is ≥2 years), whether the participant has received prior treatment for the psychosis (traditional or faith healers), whether the patient had a say in the choice of antipsychotics that was prescribed to them.We will administer the UBACC [42] to assess participant’s capacity to provide informed consent.The M.I.N.I 7.0.2 [40] psychosis, depression, bipolar affective disorders, substance use disorder, PTSD and generalized anxiety modules will be used to confirm the presence of a psychoses, and other CMD. The MINI has been used in multiple Ugandan study settings including the Neuro-GAP project, although it is yet to be validated for use in these settingsSymptom severity assessed using the YMRS [43] or PANSS [44]. Both the YMRS and PANSS have been used in Ugandan study settings although it is yet to be validated for use in these settingsThe presence of medication side effects will be assessed using the modified version of the Glasgow Antipsychotic Side Effects Scale (GASS)The World Health Organization Disability Assessment Schedule Version 2 (WHODAS 2.0) will be used to assess the level of social and occupational functioning of participants. There is limited data about the use of the WHODAS in Ugandan populations.Adherence to antipsychotics will be measured using the medication adherence rating scale (MARS) for psychosis [47].We will document mortality from any causes in the participants using the WHO verbal autopsy scale.illness management ability will be assessed using the IMR [45].The care giver burden will be measured using the short version of the burden scale for care givers (BSFC) [46].

**Table 1 pone.0268493.t001:** Summary of the study instruments to be administered at baseline and follow-up.

Instrument	Baseline	Follow-up
Consent forms, UBACC(administered a day earlier)		
Demographic parameters	Yes	No
UBACC	Yes	No
MINI	Yes	Yes
Physical exam	Yes	Yes
Symptom severity using the YMRS/PANSS	Yes	Yes
GASS	Yes	Yes
WHODAS 2.0	No	Yes
Medication adherence using the MARS	No	Yes
WHO Audit to assess all course mortality	No	Yes
Illness Management and recovery	No	Yes
BSFC (participant’s care givers only)	Yes	Yes

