### Objective

Our primary objective will be to determine the feasibility of recruiting and retaining patients with a FEP and for the secondary objective, we will determine the preliminary efficacy of psycho-education on illness self-management, stigma, adherence to medications and symptom severity.

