### Follow-up

Participant Follow-up: We shall collect the same data as at baseline from participants at month 3 then every six months. If the participant accesses health care and we are not aware, we will review their medical records and abstract information collected during the course of routine care (where they exist). However, all attempts will be made to always collect data directly from the participants.

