### Data analysis plans

We will report the duration of recruiting participants and the proportion of eligible patients who get recruited. We will compare the demographic parameters (age, gender, education status) as well as disease severity. We will compare the proportion of participants who are retained in the study at week 4, 12 and 24 as well as mean differences in adherence, stigma, illness management ability and symptom severity (PANSS or YMRS) scores between the intervention and control arms. We will use the Bonferroni approach to correct for multiple comparisons.

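### Table 1 contradicts the text on three of the four efficacy outcomes: adherence and illness management are marked as not taken at baseline, and the stigma scale has no row at all

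*Protocol article*

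**What the plan says.** All references are to the protocol article.

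- **Objective** sets the secondary aim as "preliminary efficacy of psycho-education on illness self-management, stigma, adherence to medications and symptom severity", which makes four efficacy outcomes.
- **Table 1**, under Study measurements, has one column for baseline and one for follow-up. Its entries are "Medication adherence using the MARS No Yes", "Illness Management and recovery No Yes" and "Symptom severity using the YMRS/PANSS Yes Yes". It has no row for a stigma scale. The Study measurements text, which refers the reader to Table 1, does not list one either.
- **Data collection** describes what the research assistants administer. The list includes an adherence measure, the IMR and the "Internalized Stigma of Mental Illness scale to assess for stigma", alongside demographics and the diagnostic MINI.
- **Blinding participants and RA to the study arm** schedules both arms for an "assessment using the same instruments at weeks 4, 12 and 24 at the clinic".
- **Follow-up** states: "We shall collect the same data as at baseline from participants".
- **Data analysis plans** compares "mean differences in adherence, stigma, illness management ability and symptom severity (PANSS or YMRS) scores between the intervention and control arms". It mentions neither adjustment for baseline nor its absence. The participant characteristics it names for comparison are demographics and disease severity.

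**The concern.** Table 1 is the only itemised schedule in the article. Its baseline entries for MARS and IMR are explicit negatives, so they cannot be put down to the shortening that a journal article needs. The narrative points the other way. A team working from the table and a team working from the text would collect different data on three of the four efficacy outcomes.

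The choice cannot be reversed, because a score not taken before the intervention starts cannot be recovered later. An analysis plan written afterwards cannot help either, since the question is what gets collected. Three things are at stake:

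- the precision of the between-arm comparison;
- the ability to see a chance imbalance, which matters more under the simple randomisation described in Random sequence allocation;
- planning information. Sample size estimation says the data will supply an effect size for a powered trial. Without baselines, the pilot cannot estimate the correlation between baseline and follow-up for these outcomes.

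**Working it through.** **Step 1. Table and text side by side.**

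| Efficacy outcome | Table 1, baseline | Table 1, follow-up | In the Data collection battery | In the Study measurements list |
|---|---|---|---|---|
| Symptom severity (YMRS/PANSS) | Yes | Yes | Yes | Yes |
| Adherence (MARS) | No | Yes | Yes (scale not named there) | Yes |
| Illness management (IMR) | No | Yes | Yes | Yes |
| Stigma | no row | no row | Yes | No |

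Table 1 gives a baseline for 1 of 4 outcomes, marks 2 of 4 as not taken, and omits 1 of 4. The Blinding and Follow-up sections describe follow-up as a repeat of the same instruments or data, which does not fit the MARS and IMR rows. WHODAS 2.0 shows the same pattern as MARS and IMR but is not one of the four efficacy outcomes, so it is not counted.

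**Step 2. The plan's own figure.** Sample size estimation says that 80 participants allow a 5% difference in mean scores to be detected. No SD, alpha or power is given, so this cannot be reproduced. The figures below are therefore in SD units and rest on stated assumptions.

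**Step 3. Inputs.** 40 per arm (Abstract, Methods) and 80% retention (Hypothesis) give 40 × 0.80 = 32 per arm at week 24. Assumed: two-sided alpha 0.05 before Bonferroni, 80% power, and a baseline-to-follow-up correlation ρ of 0.4 to 0.6.

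**Step 4. Detectable difference without baseline.** The normal approximation is (1.960 + 0.842) × √(2/32) = 2.802 × 0.25 = 0.70 SD. With the t distribution it is 0.711 SD, used below.

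**Step 5. With baseline adjustment.** The variance is multiplied by 1 − ρ², so the detectable difference is 0.711 × √(1 − ρ²) and the equivalent unadjusted size per arm is 32/(1 − ρ²).

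| ρ (assumed) | 1 − ρ² | Detectable difference | Equivalent n per arm |
|---|---|---|---|
| 0.4 | 0.84 | 0.652 SD | 38 |
| 0.5 | 0.75 | 0.616 SD | 43 |
| 0.6 | 0.64 | 0.569 SD | 50 |

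Data analysis plans calls for Bonferroni without giving the number of comparisons. If it is four (alpha 0.05/4 = 0.0125), the detectable difference is 0.857 SD unadjusted, and 0.785 to 0.685 SD for ρ of 0.4 to 0.6. The proportional gain is the same.

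**Step 6. Chance imbalance.** The SD of a chance baseline difference between arms is √(2/n): 0.22 SD at 40 per arm and 0.25 SD at 32. The probability of a gap larger than 0.3 SD in either direction is 2 × [1 − Φ(0.3/√(2/n))], about 18% at 40 per arm and 23% at 32. A gap of 0.3 SD would be expected to shift the follow-up difference by ρ × 0.3 = 0.12 to 0.18 SD. Without a baseline, that shift can be neither seen nor adjusted for.

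**The case against.** **The text may imply that the baselines are taken.** Three sections point that way, and Table 1 is titled a summary. This stands, and it limits the point. A reader of the table alone might infer that three outcomes have no baseline anywhere in the plan, but that is true of Table 1 only. The text does not settle the matter either. The Data collection list is not labelled as baseline and also contains retention and drop-out measures, and wording about the same data can be loose. What is certain is the conflict.

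**Stigma may well be collected.** It is a named outcome with a named scale. A reader might infer that there will be no stigma data, but the documents show only that the schedule has no place for it.

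**The analysis may already adjust for baseline.** A reader might infer that the arms will be compared on raw follow-up means. Data analysis plans does not say so, and the model may be in an analysis plan that is not shown. That silence is no error.

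**A randomised comparison does not need a baseline.** This is correct. A reader might infer that the hypothesised improvement cannot be shown without one. However, the Abstract plans to compare the groups at weeks 4, 12 and 24 by intention to treat. Under randomisation the follow-up difference estimates the effect without bias, and its standard error already allows for chance imbalance. The loss is in precision, balance checking and planning data.

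**Omitting MARS at baseline may be deliberate.** Many participants are inpatients awaiting discharge, and the first-episode definition caps prior antipsychotic use at 6 weeks in one of its criteria. A baseline adherence score may therefore say little. This is plausible, but the article does not state it, and it would not explain the IMR entry or the missing stigma row.

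**Conclusion.** The point holds as an internal contradiction on three of the four efficacy outcomes, together with a named outcome that is missing from the schedule. If Table 1 governs, baselines for adherence and illness management are irrecoverable and stigma has no scheduled visit. The between-arm comparison would remain unbiased.

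The contradiction itself rests on no assumption. The size of the precision loss is illustrative: the documents give no correlation, and 0.4 to 0.6 is assumed for every scale. On that range, going without baseline adjustment leaves the detectable difference at about 0.71 SD instead of 0.65-0.57 SD. The gain could be smaller for MARS. It could also be smaller for severity, since eligibility requires that active symptoms have resolved, which may narrow the range of baseline scores.

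Severity is moderate. Feasibility is the primary objective, efficacy is described as preliminary, and no primary outcome is affected.

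**What to change.** 1. Reconcile Table 1 with Data collection, Blinding participants and RA to the study arm, and Follow-up, so that one schedule governs.
2. Add a row for the Internalized Stigma scale to Table 1, marked at baseline and follow-up, and list the scale under Study measurements.
3. Mark IMR as Yes at baseline. Do the same for MARS, or state why a baseline adherence score is left out on purpose. Check the WHODAS 2.0 entry at the same time.
4. State in Data analysis plans, or in the analysis plan, that where a baseline exists, including for severity, the arms are compared with adjustment for the outcome's own baseline score, by ANCOVA or a linear mixed model.

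The cost is a few more questionnaires in a baseline interview that Assessing the capacity to consent already puts at no less than 120 minutes, with breaks. That is a real burden for people recovering from a first episode, though a modest one. The adjustment needs no further data. Steps 1 to 3 have to be settled before enrolment, because a missed baseline cannot be collected later.
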